## Abstract

**Introduction:**

Balance disturbances in Parkinson’s Disease (PD) are usually assessed in a single-task as well as standard balance physiotherapy is carried out in isolated environments. Conversely, daily activities are developed in highly challenging environments. Although functional balance training (FBT) is included in the latest protocols, several methodological issues have not yet been considered. In the proposed single-blinded randomized control trial with crossover (NCT04963894), the aims are (1) to quantify the effects achieved by domiciliary FBT (balanceHOME program) in participants with and without cognitive impairment, and (2) to compare them with the effects of a passive-control period and a conventional face-to-face physiotherapy program for PD.

**Methods:**

The initial recruitment was estimated at 112 people with idiopathic PD. Two-thirds of the participants will be randomized to one of the two groups to make the crossover. In contrast, the other third will do a face-to-face group program only. The balanceHOME protocol consists of challenging balance exercises incorporated into functional daily tasks, developed in-home and conducted two times per week for 60-min over an 8-weeks period. The primary strategy will consist of splitting functional tasks of daily life into static and dynamic balance components, besides standardized facilitate and disturbing strategies to execution of each exercise. Biomechanics and clinical performance of balance and gait, perception of quality of life, cognitive and mental functioning, and severity of PD will be measured at baseline (T0), post-8 weeks training (T1), and follow-up (T2).

**Results:**

The primary outcome of the study will be the center of pressure sway area. The secondary outcomes consist of biomechanics and clinical variables related to static and dynamic balance. Outcomes from biomechanical of gait, quality of life, cognitive and mental state, and severity of PD, represent the tertiary outcomes.

**Discussion:**

The balanceHOME program standardizes the FBT in demanding and daily environments for people with PD who prefer individualized treatment from home. This is the first time that the effects of group versus individual balance rehabilitation have been compared in people with and without cognitive impairment and evaluated in complex environments. This still-to-be-finished study will open the possibility of new strategies according to changes in post-pandemic therapeutic approaches.

## Introduction

1.

Parkinson’s disease (PD) is a progressive neurodegenerative disease characterized by motor and non-motor symptoms, including bradykinesia, resting tremor, muscle rigidity, flexion posture, walking and balance impairment, autonomic dysfunctions, sleep disorders, cognitive disturbances, and behavioral alterations (Poewe et al., 2017). The balance disturbances in PD consist of biomechanical restrictions on support base width, postural misalignment, muscle weakness at the ankle and hip for standing, limits of stability (LoS) restriction (Kara et al., 2012; Soke et al., 2019) perception of verticality loss, absence or delay of anticipatory postural adjustments, impaired sensorimotor integration, poor control of the center of pressure (CoP) (Carpinella et al., 2017; Santos et al., 2017), loss of dynamic balance during walking (Wong-Yu and Mak, 2015a; Klamroth et al., 2016; Fil-Balkan et al., 2018; Giardini et al., 2018), and gait speed decrease (Conradsson et al., 2015; Giardini et al., 2018; Wallén et al., 2018). As a result of these disturbances, the risk to fall forward (propulsion) or backward (retropulsion) appears, which increases with the PD progression (Allen et al., 2011; Park et al., 2015; Yitayeh and Teshome, 2016; Hubble et al., 2018). Consequently, these events affect a wide range of daily life activities and participation (World Health Organization (WHO), 2001), impacting functional independence and the quality of life of people with PD (da Capato et al., 2015; Park et al., 2015; Yitayeh and Teshome, 2016).

Balance alterations in PD are usually assessed in a single task. The most common tests are based on static and dynamic balance, where the patient controls the CoP in a static position (e.g., standing) (Negrini et al., 2017; Giardini et al., 2018; Soke et al., 2019) or during motion in direction to the different LoS (Kara et al., 2012; Carpinella et al., 2017; Soke et al., 2019). To this assessment methodology, it is common to add the blockade of the different systems that participate in balance regulation, either by closing the eyes or placing foam under the feet. Similarly, standard balance physiotherapy is carried out in isolated environments with exercises focused on single tasks or similar scenarios to those of the evaluation (Giardini et al., 2018). Conversely, daily activities are developed in highly challenging environments, which have been addressed in previous publications with Wii balance games (Yen et al., 2011; Zalecki et al., 2013; Carpinella et al., 2017; Negrini et al., 2017; Feng et al., 2019; Yuan et al., 2020), dual-task exercises within daily activities (Conradsson et al., 2015; Wong-Yu and Mak, 2015a, 2015b; Atterbury and Welman, 2017; Perumal et al., 2017; Santos et al., 2017; Wallén et al., 2018; Leavy et al., 2020), and single daily activities training (Smania et al., 2010; Kara et al., 2012b) including postural transferences (Millage et al., 2017; Soke et al., 2019). Although functional balance training (FBT) is included in the latest protocols, which consists of daily activities with feasible settings for older adults with PD, there are several methodological issues that have not yet been considered. One of these is the assessment methodology of the previous studies and the objectivity of the measurements, using in most cases, scales, and clinical tests only (Conradsson et al., 2015; Wong-Yu and Mak, 2015a,b; Atterbury and Welman, 2017; Perumal et al., 2017; Santos et al., 2017; Wallén et al., 2018; Leavy et al., 2020) instead of integrating biomechanical parameters of balance in different measurement conditions with a follow-up period after finishing the studied intervention (Kara et al., 2012b; Conradsson et al., 2015; Atterbury and Welman, 2017; Perumal et al., 2017; Santos et al., 2017; Soke et al., 2019; Leavy et al., 2020). Furthermore, the authors who inform significant improvement in balance biomechanics (Kara et al., 2012; Santos et al., 2017; Soke et al., 2019) do so in patients with normal cognition status and use habitual locations like a physiotherapy gym or hospital facilities. To respond to the challenges that emerged since the COVID-19 pandemic, such as the demand for rehabilitation programs that can be followed from home, the effect of domiciliary FBT and the long-term impact with adequate follow-up need still be determined, as well as the effects in people with PD in advanced stages where cognition is altered. For the foregoing, the aims of this study are (1) to quantify the effects achieved by domiciliary FBT on the biomechanics of balance, gait, perception of quality of life, cognitive and mental performance, and severity of PD in participants with and without cognitive impairment and (2) to compare them with the effects of a passive-control period and a conventional face-to-face physiotherapy program for PD. We hypothesized that balance home training based on functional exercises has a greater effect than the traditional physiotherapy group. If this hypothesis is confirmed, it will open the possibility of new rehabilitation strategies according to changes in post-pandemic therapeutic approaches, reducing morbidity, and saving costs to the healthcare system.

## Materials and analysis

2.

### Study design

2.1.

The balanceHOME trial is designed as a randomized, controlled, and blind evaluator trial with a crossover intervention group. To write this protocol was used as a guide the Standard Protocol Items for Randomized Trials (SPIRIT) guidelines (Chan et al., 2013) and the Consolidated Standards of Reporting Trials statement for randomized controlled trials (Moher et al., 2010). The SPIRIT guidelines can be consulted in Supplementary material 1. Once the study was designed, it was registered on ClinicalTrials.gov (NCT04963894) on 15 July 2021 with the approval information of the Human Research Ethics Committee of the Experimental Research Ethics Commission of the University of Valencia obtained (Supplementary material 2).

The balanceHOME will be started with a baseline assessment session (T0) and followed by random allocation to one of two study groups: the experimental group (EG) or the passive control group (PCG). Additionally, a third group of participants with PD who habitually developed a conventional group physiotherapy program (Active Control Group, ACG) will be included in the evaluation process. At the end of the interventions (8 weeks), a post-training evaluation (T1) will be carried out, and subsequently, a follow-up assessment (T2) 8 weeks after the physiotherapy programs have finished. At this point, patients from PCG will switch with EG to receive the functional balance home program. The EG will follow a 4-month washout period (Serrao et al., 2019) before continuing as passive control participants (see Figure 1). The crossover design allows to control the intra-individual changes (due to personal characteristics and disease presentation), offer all the research benefits to the participants, and maximize the sample size it can achieve.

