#### Setting and eligibility criteria

2.2.1.

The recruitment of participants, the eligibility criteria assessment, obtaining informed consent (Supplementary material 3), and the intervention of the ACG will be carried out in the facilities of the neurorehabilitation center participant in the study. On the other hand, the pre-intervention, post-intervention, and 8-week follow-up evaluations will be carried out at the University of Valencia, while the interventions of the EG will be carried out at each participant’s home.

The recruitment and eligibility criteria assessments will be carried out by two different physiotherapists, who will verify the following inclusion criteria: (i) idiopathic PD; (ii) Hoehn & Yahr stage I-IV; (iii) independent gait with or without technical assistance; and (iv) stable parkinsonian medication for at least a month before the study star. On the contrary, the exclusion criteria will be as follows: (i) comorbidities that affect balance or walking; (ii) other neurological pathologies besides PD; (iii) chronic diseases not medically controlled; and (iv) participation in another physiotherapy program or sport activity during the intervention period or in the month before starting the study. Patient enrolment was started in August 2021 and is expected to be completed in August 2023. All patients are expected to have completed baseline testing in September 2023.

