### Assignment of interventions and blinding

2.3.

An external investigator will perform the randomization process (1:1). Stratified randomization will be carried out according to PD severity and general cognitive state and assigned to one of the two groups for crossover, EG or PCG. A matched-pairs design will be created in which participants were allocated to these two groups taking into consideration the outcomes, i.e., Hoehn and Yahr state (I-II-III-IV) and Mini Mental Parkinson Test score (≥ 25, normal cognitive function or ≤ 24, altered cognitive function) at T0. The principal investigators will be responsible for the management of participants’ appointments after being assigned by telephone. On the other hand, the physiotherapist evaluator will be blinded to the assignment of the groups. For this reason, it will be explained to the participants that they do not reveal information about their intervention during the assessment sessions. Due to the nature of interventions, the patients and the physiotherapist who develop the rehabilitation cannot be blind to the treatment to be performed, but the hypothesis of the study will be hidden. Additionally, after the consent signature, participants will be assigned a numeric code to hide the group of intervention.

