### Data collection, management, and statistical analysis

2.4.

Both evaluators (physiotherapist and neuropsychologist) will be responsible for exporting and filling in a database with variables from the scales and tests mentioned in Table 2 according to the code assigned to each patient to ensure his or her anonymity. To protect confidentiality during the study, the personal information of participants will be located separately from the main dataset on a local computer. The raw dataset will be maintained for 10 years after the completion of the trial with indefinite restricted access due to sensitive data. After the publication of the results trial, a fully anonymized patient-level dataset will be made publicly available on the registration trial website (clinicaltrials.gov). For participation in this study, no participant will receive any kind of incentives or compensation.

All analyses will be evaluated by intention-to-treat principles in terms of assignment to treatment and used a level of significance of 0.05. There are no interim analyses planned for this study. We will use the statistical software SPSS Statistics version 24.0 (IBM Corporation) for all the statistical analyses. Categorical variables were presented using frequency and percentage, and continuous variables as mean with standard deviation if they follow a normal distribution. To test for possible carryover effects of the experimental group, the sum of the values measured in the two periods for each subject will be calculated and compared across the two randomized groups (EG and PCG) using a test for independent samples (Serrao et al., 2019). There should be no difference if there is no sequence (balanceHOME program—usual daily activity or usual daily activity—balanceHOME program) effect.

To answer to the main aim of the study, a two-factor mixed multivariate analysis of variance (MANOVA) test was conducted to analyze the effects of within-subject factors (assessment times) and the between-subject factor (group) on the outcomes registered. The Bonferroni adjustment was used for *post-hoc* comparisons, and differences were declared statistically significant if the value of *p* was less than 0.05. Differences between groups for demographic outcomes were verified with a univariate analysis of variance (ANOVA) between-subjects test. Furthermore, to test for sex differences between groups, a chi-square analysis was used (San Martín Valenzuela et al., 2020b).

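### The only stated hypothesis, balanceHOME against conventional group physiotherapy, rests on a non-randomised group of habitual attenders analysed without adjustment for confounders

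*Protocol article*

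**What the plan says.** The Introduction gives a single hypothesis: "We hypothesized that balance home training based on functional exercises has a greater effect than the traditional physiotherapy group". That is EG against ACG. The second aim also includes a comparison with the passive-control period, but no hypothesis is attached to it.

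The Study design section randomises participants to EG or PCG and then adds the ACG, described as "a third group of participants with PD who habitually developed a conventional group physiotherapy program". The section on assignment confirms that participants are randomised 1:1 and "assigned to one of the two groups for crossover, EG or PCG". The matching on Hoehn & Yahr stage and Mini Mental Parkinson (MMP) class has the same limit: "participants were allocated to these two groups taking into consideration the outcomes". The abstract agrees that a third of the sample lies outside the randomisation: "In contrast, the other third will do a face-to-face group program only".

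The sample size section nevertheless powers the trial on differences among all three groups. For the main aim, section 2.4 fixes a two-factor mixed MANOVA (assessment time and group) with Bonferroni post-hoc comparisons and names no covariate. Group comparability is only tested, by chi-square for sex and otherwise as follows: "Differences between groups for demographic outcomes were verified with a univariate analysis of variance (ANOVA) between-subjects test".

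Exclusion criterion (iv) in section 2.2.1 rules out "participation in another physiotherapy program or sport activity during the intervention period or in the month before starting the study". The article does not say how this applies to people who join the ACG because they habitually attend such a programme.

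**The concern.** Randomisation makes EG and PCG comparable. Nothing does this for EG and ACG, yet the model treats the three groups alike. Two things can distort the EG–ACG contrast.

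- **Confounding of change.** People who habitually attend a group programme may differ from the randomised participants in severity, cognition, mobility or motivation, and so in how much they change over 8 weeks.
- **A different meaning of T0.** If ACG members already carry some of their programme's benefit at T0, they have less left to gain by T1. The contrast then moves towards balanceHOME against no treatment.

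A significance test on demographics neither detects nor corrects either of these reliably. At stake is the trial's one hypothesis, together with the abstract's claim about group versus individual rehabilitation.

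**Working it through.** **1. The plan's own figure.** Inputs from section 2.2.4: three groups, f = 0.15, two-sided 5%, 95% power, N = 93, and 112 after 20% dropout. The number of measurements m and their correlation ρ are not given. I assumed ρ = 0.5, sphericity and the repeated-measures interaction test:

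λ = f²·N·m/(1 − ρ), df1 = (k − 1)(m − 1), df2 = (N − k)(m − 1).

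- With k = 3 and m = 6 (two phases of three assessments): λ = 0.0225 × 93 × 6/0.5 = 25.11, df = 10 and 450. The smallest N for 95% power is 93, the stated figure.
- With k = 3 and m = 3 (one phase): λ = 12.56, df = 4 and 180. Power at 93 is 81%, and 95% needs 141.
- Dropout: 93 × 1.2 = 111.6, rounded up to 112.

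The first match rests on assumed inputs and need not be how the figure was obtained. It is consistent with the text in counting the non-randomised ACG as a full comparison group. The present point does not depend on it.

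**2. What the time-by-group term estimates.** Score improvement as positive. Assume:

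- both programmes have the same full effect d, in SD of change;
- a share s of that effect is already present in the ACG at T0 and none is present in the EG;
- background change is equal and there is no other selection.

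| | T0 | T1 | Change |
|---|---|---|---|
| EG | 0 | d | d |
| ACG | s·d | d | (1 − s)·d |

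The change-score difference is d − (1 − s)·d = s·d, although the programmes are equal. It is 0 at s = 0 and d at s = 1. Adjusting T1 for T0 with slope b gives 0 − b·(0 − s·d) = b·s·d. Comparing T1 levels gives 0, or a difference in favour of the ACG if longer training has taken it beyond d. The answer therefore depends on the analysis chosen, and the documents give no value for s.

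**3. Illustration of the consequence.** Take 93/3 = 31 per group and a two-sided t-test on change with 60 degrees of freedom. The noncentrality is d·s·√(31/2) = 3.937·d·s. For example, d = 0.5 and s = 1 gives 1.97, against a critical value of 2.00. The table shows the probability of a significant result favouring balanceHOME when the programmes are equal. The nominal values are 2.5% at α = 0.05 and 0.8% at α = 0.05/3.

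| d (assumed) | s = 0 | s = 0.5 | s = 1 | s = 0.5, α = 0.05/3 | s = 1, α = 0.05/3 |
|---|---|---|---|---|---|
| 0.3 | 2.5% | 8% | 21% | 4% | 11% |
| 0.5 | 2.5% | 16% | 49% | 8% | 32% |
| 0.8 | 2.5% | 34% | 87% | 20% | 75% |

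The values of d and s are illustrative and do not come from the protocol.

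**4. Study design against criterion (iv).** If criterion (iv) binds the ACG, its members have had a month without the programme before T0 and s may be small. If they are exempt because the criterion speaks of *another* programme, their T0 is on-treatment while that of EG and PCG is not. The article supports either reading, so the meaning of the ACG's T0 is not fixed.

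**The case against.** The best defence has five parts.

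- **Direction.** No passage gives the ACG's training status at T0. The standard programme is described as an 8-week block with a start and an end, and criterion (iv) carries no stated exemption. This stands. A reader might infer that the design certainly favours balanceHOME. The documents do not show it: selection can act either way, and comparing levels at T1 or T2 could favour the ACG.
- **Eligibility.** A reader might infer an outright contradiction between habitual attendance and criterion (iv). Because the criterion excludes *another* programme, this is an ambiguity to clear up and not a proven conflict.
- **Adjustment.** T0 is a level of the time factor, so the interaction does compare change from baseline, and covariate lists are often left to an analysis plan. The first part stands, but comparing change removes neither confounding of change nor a plateau. The second part helps little, because the article itself fixes the model for the main aim and applies it to all three groups alike.
- **Openness.** The article says plainly that only two groups are randomised, so it does not follow that the EG–ACG result would be presented as a randomised finding. Nor does the article describe the ACG as drawn from a different centre.
- **Scope.** The passive-control part of the second aim is randomised and untouched. This stands.

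It is also tempting to size the bias at 0.3 SD by doubling f = 0.15. That conversion holds for two equal groups. In a three-group repeated-measures calculation, f does not map to one pairwise difference, and no figure in the article gives the prior effect of the conventional programme.

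**Conclusion.** The point holds as a statement about what the comparison can support. The trial's only hypothesis is addressed by a contrast that is neither randomised, stratified nor matched, against habitual attenders, in a model without confounder adjustment. Following the plan as written gives a potentially confounded answer to its own hypothesis. Bias is likely, and on change scores it plausibly favours balanceHOME. Through the prior-training mechanism its size is s·d, from zero to the whole prior programme effect, and confounding by selection may add to or offset this. The error rates shown rest on assumed values of d and s, equal background change and 31 per group. They illustrate the scale and are not estimates for this trial. A contrast whose bias has an unknown sign cannot carry a superiority claim. This point does not affect EG against PCG.

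**What to change.** 1. Name EG versus PCG as the randomised, confirmatory comparison.
2. Label EG versus ACG non-randomised and secondary. Adjust it for Hoehn & Yahr stage, MMP class, age and sex. Show T0-adjusted and change-score versions side by side as a sensitivity check, since step 2 of the working shows that they can differ. Do not add prior physiotherapy exposure as a covariate: it would nearly duplicate group, and the article does not show that it is collected.
3. Reconcile Study design with section 2.2.1 by stating whether criterion (iv) applies to the ACG, and so whether its T0 is on-treatment.
4. Word the hypothesis in the Introduction and the abstract's group-versus-individual claim as a non-randomised comparison.

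The cost is small. Hoehn & Yahr and MMP are scheduled at T0, and sex is already in the planned group tests. Age is not named in the article but should be available with the demographic data. The real price is a weaker claim on the active comparison, and adjustment for these four variables will not remove unmeasured selection.
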